### Long-term follow-up data

To provide early data on the sustainability of weight change and inform selection of longer-term outcomes for a definitive trial, we will collect routine clinical weight and lung function data for up to 2 years after completion of the 24-week study period. Participants will be asked for optional consent at enrolment for access to these routine data and to confirm that their CF centre may be contacted for data extraction where required.

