### Study procedures and participant flow

All study visits will be conducted remotely via Microsoft Teams or equivalent to minimise participant burden and assess the feasibility of home measurements. The baseline assessment will last approximately 60 min and follow-up assessments 15–20 min. Technical support to help participants access Microsoft Teams will be provided where required. Informed consent will be obtained remotely by a delegated member of the local research team. Eligibility will then be confirmed, and baseline assessments will be conducted using home monitoring equipment posted to the participant prior to the baseline assessment and a returned blood sample kit. Once all baseline measurements are finalised, participants will be randomised. Those allocated to the routine care group will follow the local standard care pathway attending their CF appointments. Participants in the intervention group will attend an initial dietetic consultation to receive intervention materials and commence the intervention. Remote assessments will take place at 4, 12 and 24 weeks. Intervention participants will participate in a qualitative interview at 12 or 24 weeks, and routine care participants will have a qualitative interview at 24 weeks. Weight and lung function data will be obtained from routine clinical records, including data collected as part of standard care and reported to the UK CF Registry, for up to 2 years post-study. Participant flow is shown in figure 1.

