### Schedule of study events

Table 1 provides a schedule of study events.

**Table 1 T1:** Schedule of study events

Procedures	Assessments				6 months after last study visit	Up to 2 years after last study visit
	0 weeks	4 weeks	12 weeks	24 weeks		
	Screening/ baseline	Assessment 1	Assessment 2	Assessment 3		
Informed consent	x					
Eligibility assessment	x					
Demographic questionnaire	x					
Medical history	x					
Concomitant medications	x	x	x	x		
Randomisation	x					
EQ-5D-5L questionnaire	x			x		
AWESCORE questionnaire	x			x		
Weight and fat/fat-free mass	x	x	x	x		
Height	x					
Blood pressure	x			x		
Five times sit-to-stand	x	x	x	x		
Lung function	x	x	x	x		
Lipid profile	x			x		
HbA1c	x			x		
Adverse events assessments	x	x	x	x		
Qualitative interview with participants			x	x		
Qualitative interviews with staff				x		
Feedback questionnaire end of trial (all participants)				x		
Feedback questionnaire end of trial (intervention participants)				x		
Fidelity of intervention delivery		x	x	x		
Additional interview with intervention participants 6 months after the last visit (optional)					x	
Follow-up through medical notes						x

EQ-5D-5L, EuroQol 5-dimension 5-level.

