### Physical measurements

All assessments will be conducted during a video call to allow researcher guidance. Height will be obtained from medical records or self-reported if unavailable. Participants will measure body weight barefoot and in light clothing using a calibrated digital scale and body composition (fat-free mass and fat mass) using a bioelectrical impedance analyser (BC-730 Tanita, Japan). Participants will be provided with standardised instructions to undertake measurements after voiding and under consistent conditions where possible, including in similar clothing. Body composition measurements will be considered exploratory and interpreted with appropriate caution given the known limitations of bioelectrical impedance analysis. Physical function will be assessed using the 5-times sit-to-stand test.^37^ Participants will measure their blood pressure at home using a validated monitor (Omron 10, Japan) following standard blood pressure measurement guidance.^38^ Spirometry will be performed according to British Thoracic Society guidelines^39^ using a home spirometer (MIR Spirobank Smart, Italy). Blood sample HbA1c and lipid profile will be assessed at baseline and 24 weeks using a home finger-prick blood sampling kit that participants will post to an established laboratory provider (Medichecks, UK). Where available, results obtained at the CF centre within 1 month of the baseline or 24-week visit will be used.

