#### Exploratory outcomes

Exploratory outcomes detailed below will be collected to inform suitable outcomes for a future definitive RCT.

Body weight and body composition (weight, fat-free mass and fat mass) using provided scales (Tanita) at home at baseline, 4, 12 and 24 weeks.Health-related quality of life using the EuroQol health questionnaire (EQ-5D-5L)^40^ and AWESCORE^41^ (CF-specific quality of life score) at baseline and 24 weeks.Lung function (forced expiratory volume predicted (FEV1%) and forced vital capacity predicted (FVC%)) measured using home spirometry at baseline, 4, 12 and 24 weeks.Physical function measured using the Five Times Sit to Stand Test^37^ observed on a video call at baseline, 4, 12 and 24 weeks.Respiratory exacerbation rate recorded as adverse events during the study.Blood pressure using home blood pressure monitors at baseline and 24 weeks.Glycaemic control – HbA1c using a home blood test kit at baseline and 24 weeks.Blood lipid profile (total cholesterol, HDL, LDL and non-fasting triglycerides) assessed at baseline and 24 weeks using a home blood test kit.Adverse events in the intervention arm which are judged to be related and unexpected.

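### Routine clinic weight and lung function are described only for after the study, while baseline and week-24 values are home readings, so a clinic-home difference could mimic or mask long-term change

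*Protocol article*

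**What the plan says.** **During the study.** Under Exploratory outcomes, weight is taken "using provided scales (Tanita) at home at baseline, 4, 12 and 24 weeks" and lung function is "measured using home spirometry at baseline, 4, 12 and 24 weeks". The Physical measurements section fixes the home conditions: "Participants will measure body weight barefoot and in light clothing using a calibrated digital scale". It also names a home spirometer.

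**After the study.** The Long-term follow-up data section gives the purpose, "To provide early data on the sustainability of weight change and inform selection of longer-term outcomes for a definitive trial", and the source and period, "we will collect routine clinical weight and lung function data for up to 2 years after completion of the 24-week study period". Study procedures and participant flow describes the same routine data, including data "reported to the UK CF Registry, for up to 2 years post-study". In Table 1 the row "Follow-up through medical notes" is marked once, in the column for up to 2 years after the last study visit. It is not marked at 0, 4, 12 or 24 weeks.

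**Possible links between the two.** Physical measurements lets CF-centre results within 1 month of baseline or week 24 be used where they exist. That sentence directly follows the one on HbA1c and lipids, and it names neither weight nor spirometry. The inclusion criteria call for an FEV1 recorded in the previous 6 months, but only to decide eligibility. No paired home and clinic reading is described.

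**The concern.** Whether weight change is sustained is a within-person question: where is this person now, compared with where they started and where they finished the programme? As described, the starting and finishing values come from one source (home devices, barefoot, light clothing) and every later value from another (routine clinic records). A systematic clinic-home difference does not average out within an arm. It is added to each person's apparent change.

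For weight, the difference could look like regain or hide it. For lung function, it could look like decline or improvement, or hide either. The protocol itself names lung function as a worry with intentional weight loss in this population, so a spurious shift could mislead the choice of longer-term outcomes for the definitive trial, which is one of the two stated uses of these data.

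**Working it through.** The plan gives no figure on this point, so there is none to reproduce. The check traces the source of each measurement and then works out what follows.

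**Step 1: source by time point**

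| Time | Weight | Lung function | Where stated |
|---|---|---|---|
| 0, 4, 12, 24 weeks | Home scale | Home spirometer | Physical measurements; Exploratory outcomes |
| After week 24, up to 2 years | Routine clinic record | Routine clinic record | Long-term follow-up data; Study procedures; Table 1 |
| Clinic value at 0 or 24 weeks | Not described | Not described (eligibility FEV1 only) | – |

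**Step 2: what each comparison contains**

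Let T be the true value and d the systematic clinic-minus-home difference. A home reading is T and a clinic reading is T + d, each with random error.

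- Clinic follow-up minus home week 24: (T_follow-up + d) − T_24 = true change + d. The same holds with home baseline as the reference.
- Clinic follow-up minus clinic week 24: (T_follow-up + d) − (T_24 + d) = true change.
- Later clinic minus first post-study clinic value: true change over that interval, with no d.

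For FEV1 or FVC in % predicted, d percentage points add d points to the apparent change.

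**Step 3: size for weight**

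The documents do not give d. Assumption for illustration: d between 0.5 and 2 kg in absolute size. The programme's target is a loss of 5% to 10%.

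Share of the loss = d / (loss fraction × weight).

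- 80 kg, 5% loss = 4 kg: 0.5/4 = 12.5%; 1/4 = 25%; 2/4 = 50%.
- 80 kg, 10% loss = 8 kg: 0.5/8 = 6.25%; 2/8 = 25%.
- BMI 27 and height 1.70 m: 27 × 1.70² = 78.0 kg, 5% = 3.9 kg; 0.5, 1 and 2 kg are 13%, 26% and 51% of it.
- Heights 1.60 to 1.80 m and BMI 27 to 30: 1 kg is 21% to 29% of a 5% loss.

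The sign matters. With d = +1 kg and no true change since week 24, 1 kg of regain appears. With d = −1 kg and 1 kg of true regain, none appears.

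**Step 4: within arm against between arms**

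If d is the same on average in both arms, the between-arm contrast contains d − d = 0 in expectation. A simulation confirms this (20 against 10 participants, no true change, assumed SD of change 4 kg, 20,000 repeats). With d = 1 kg, the mean within-arm change was 1.01 kg (intervention) and 1.00 kg (routine care), and the between-arm difference was 0.01 kg.

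**The case against.** A fair defence has several parts.

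- **The plan defines no long-term change score.** The Statistical analysis section does not mention these data, and the choice of reference value may sit in a fuller document. A reader might infer that the plan commits to subtracting home from clinic values. It does not. What stands is that the period of extraction is stated in three places, each time as post-study, and on that description no clinic reference at baseline or week 24 is available to choose.
- **The wording sets an end point and does not expressly exclude earlier records.** True, so the remedy is a clarifying sentence. But the schedule and both text passages point the same way.
- **A same-source comparison remains.** Routine dietetic contact is typically every 3 months and continues for intervention participants. If weight is recorded then, later clinic values can be set against the first post-study one. It would therefore be too strong to say that nothing about sustainability can be read. What is lost is the first interval after week 24 and the link back to baseline.
- **The randomised contrast is largely protected.** This stands, if the difference is similar in both arms (Step 4).
- **The safety stakes are limited.** A reader might infer that the trial's safety assessment is compromised. It is not: safety is judged on adverse events, with reporting ending at 24 weeks, and post-study lung function enters no progression criterion.
- **The CF-centre clause might supply clinic values.** Its placement suggests blood results. If it did extend to weight and spirometry, it would replace some home readings and not others, mixing sources at the reference points without linking them.

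**Conclusion.** The point holds as a minor, inexpensive improvement. As described, change from baseline or week 24 into the follow-up period would compare clinic with home readings, and a systematic difference between them would enter the within-arm change in full.

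The size is illustrative only, because it rests on the assumed 0.5 to 2 kg. The direction is unknown, so the documents do not support saying that the data will show false regain or false decline; they could equally conceal either. No figure can be put on the lung-function difference from the documents. The sample size, the progression criteria and the safety assessment are unaffected, and the data depend on optional consent from at most the 30 planned participants.

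**What to change.** Add to the Long-term follow-up data section wording such as: *The same record extraction will also take the clinic weight, FEV1 and FVC nearest before randomisation and nearest the 24-week visit, within a pre-stated window, with their dates. Long-term change will be calculated from clinic value to clinic value. The optional records consent covers this earlier period.* Mark the extraction accordingly in Table 1.

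The length of the window is for the study team to set. Agreement between home and clinic readings at the two time points could be reported as a by-product and would help in choosing outcomes for the definitive trial.

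**Cost:** two more dates per participant in an extraction already planned, and a check of the consent wording, which is easiest to settle early because that consent is taken at enrolment. Some participants will have no clinic value in the window, and values not taken on the visit date carry some timing error.

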### Outcomes

#### Primary feasibility outcomes

The primary objective of this study is to assess the feasibility of progression to a definitive RCT. The following progression criteria will determine whether to proceed to a full RCT without changes (green), proceed with amendments (amber) or not proceed (red) (table 2).

**Table 2 T2:** Progression criteria for feasibility outcomes

Criterion	Measure	Green (progress)	Amber (progress with modifications)	Red (stop – do not proceed to definitive trial)
Recruitment	1a Rate (*n* of patients per site per month)	≥0.6	0.35–0.59	≤0.35
Recruitment	1b Total *N* participants recruited	≥30	16–29 (consider adding sites)	15
Engagement	Proportion of participants who attended ten or more sessions during the 24 weeks (60% of sessions) and at least one of the last three sessions.	≥60%	36%–59% (consider modifying based on process evaluation)	≤35%
Adherence	Proportion of participants in the intervention group with ≥5% wt loss at 12 weeks	≥50%	36%–49%	≤35%
Retention	Proportion of randomised participants completing a 24-week follow-up visit	≥75%	51%–74%	≤50%
Safety	Safety profile	Adjudicated by the Study Steering Committee, based on AE and SAE in the intervention arm which are related and unexpected		

AE, adverse event; SAE, serious AE.

**Recruitment rate per month and overall recruitment:** assessed using the number of sites open, the total number of participants recruited, and the number of participants recruited per site.**Engagement rate:** assessed using the proportion of participants who attended ten or more sessions during the 24 weeks (60% of sessions), inclusive of at least one of the last three sessions.**Adherence rate:** assessed using the proportion of intervention participants with ≥5% wt loss at 12 weeks. The ≥5% wt loss threshold at 12 weeks reflects a clinically meaningful benchmark commonly used in weight management studies and provides an early signal of intervention response. Additional data will include attendance at scheduled dietetic appointments, self-reported adherence to the meal replacement/provided meals components and ordering data.**Retention rate:** assessed using the proportion of randomised participants completing a 24-week follow-up visit measured using data documented in the study notes at one time point.**Safety profile:** assessed using adverse events and serious adverse events in the intervention arm that are related and unexpected.

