### Recruitment

Participants will be recruited from four UK CF centres over a period of 12 months; centres were identified via an expression of interest and feasibility assessment coordinated by the UK CF Trust Clinical Trials Accelerator Platform team. Sites were selected based on dietetic and research staff capacity and geographical representation. Established patient cohorts enable database screening to identify potentially eligible participants. Reasons for declining participation will be recorded using a predefined list in the screening log to inform assessment of recruitment feasibility.

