### Sample size

The study aims to recruit 30 participants (20 intervention, 10 routine care). As this is a feasibility study, it is not powered to detect a clinically or statistically significant difference between groups.^25^ The sample size was not arrived at using a statistical method but was informed by guidance to estimate key feasibility criteria with sufficient precision to inform progression decisions and the design of a definitive trial.^26^ The 2:1 allocation ratio allows greater experience of the intervention while retaining a comparator group to assess feasibility processes.

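### Table 2's two recruitment criteria disagree at 16 and 29 participants over the planned 48 site-months, and a rate of 0.35 is both amber and red

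*Protocol article*

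**What the plan says.** Under Recruitment, participants are to be "recruited from four UK CF centres over a period of 12 months". The Sample size section sets the target: "The study aims to recruit 30 participants (20 intervention, 10 routine care".

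Under Primary feasibility outcomes, the article gives the table decision-making force: "The following progression criteria will determine whether to proceed to a full RCT without changes (green), proceed with amendments (amber) or not proceed (red". Recruitment has two rows in Table 2:

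- Criterion 1a, "Rate (*n* of patients per site per month": green ≥0.6, amber 0.35–0.59, red ≤0.35.
- "1b Total *N* participants recruited": green ≥30, amber "16–29 (consider adding sites", red 15.

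The red column means that the definitive trial does not go ahead. The text below the table says that the recruitment assessment takes account of how many sites are open, the total recruited and the number per site. It gives no rule for combining the two rows.

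**The concern.** The primary objective is the progression decision, so Table 2 is the trial's main decision rule. Once the number of sites and months is fixed, a rate and a total carry the same information, and their cut-offs should translate into each other. If they do not, one recruitment result receives two pre-specified answers. The case that matters most is a total that is red on one row and amber on the other, because one row then says stop and the other says proceed with changes. With no stated precedence, the document leaves that choice open at exactly the point where the table is meant to settle it.

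**Working it through.** **Inputs.** Four sites and 12 months (Recruitment); target 30 (Sample size); bands for 1a and 1b (Table 2). The red entry for 1b is read as 15 or fewer. The bare figure is not treated as an error.

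**Denominator.** Site-months = 4 × 12 = 48, if every site is open for the whole period.

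**Reproducing the target.** Total = rate × site-months, so the green rate gives 0.6 × 48 = 28.8, that is 29 participants. In reverse, 30 / 48 = 0.625. The plan's target and its green rate agree to within about one participant but are not the same cut-off.

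**Red boundary.** 0.35 × 48 = 16.8, so 1a is red up to 16 participants. Row 1b is red only up to 15, and 15 / 48 = 0.3125.

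**Totals near the boundaries at 48 site-months.**

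| Total | Rate | 1a | 1b |
|---|---|---|---|
| 15 | 0.3125 | red | red |
| 16 | 0.333 | red | amber |
| 17 | 0.354 | amber; amber and red if rounded to 0.35 | amber |
| 29 | 0.604 | green | amber |
| 30 | 0.625 | green | green |

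Every other total from 10 to 35 has the same colour on both rows.

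**Overlap within 1a.** The value 0.35 is included in both amber and red. At 48 site-months it cannot occur exactly, because it would need 16.8 participants, so it matters there only through rounding of 17 / 48. It can occur exactly with other denominators, for example 14 / 40 = 0.35.

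**Fewer site-months.** The article gives no opening dates, so these figures are assumptions that show a range:

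- 40 site-months (average delay of two months, 4 × 10): totals of 24–29 are green on 1a and amber on 1b; 15 (0.375) is amber on 1a and red on 1b.
- 36 site-months (average delay of three months, 4 × 9): totals of 22–29 are green on 1a and amber on 1b; 13–15 are amber on 1a and red on 1b.
- 24 site-months (average delay of six months, 4 × 6): a total of 15 gives 15 / 24 = 0.625, green on 1a and red on 1b.

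**The case against.** The strongest reply is that the rows measure different things: yield per open site, and what the study delivered. A green rate with an amber total is then coherent. Sites recruit well but there were too few site-months, and the amber cell of 1b itself suggests adding sites. This stands for most of the green/amber disagreement under late opening. It does not explain a total of 16 at full opening, where the rate says stop and the total says proceed with changes, nor the double listing of 0.35.

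It is also fair that the effect is small at the planned 48 site-months: two totals, plus 17 by rounding. The green mismatch is a single participant, and 0.625 is 0.6 at the one decimal printed. No hypothesis test or effect estimate depends on it, an independent steering committee oversees the study, and qualitative findings support interpretation. A fuller protocol may also say how the rows combine.

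Three stronger readings are tempting but not supported:

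- A reader might infer that the rate bands overlap generally. They overlap only at 0.35. The green/amber disagreement arises between 1a and 1b, not within 1a.
- A reader might infer that the choice between rows will be made after the results are known. The article shows no rule, but that does not establish that none exists.
- A reader might infer that the percentage rows of Table 2 have gaps, since 6/17 = 35.3%, 13/22 = 59.1% and 20/27 = 74.1% lie between the printed limits. Rounded to whole percentages, as the table is printed, each falls in one band. At the planned 20 intervention and 30 total participants no gap arises even without rounding: for example, 7/20 = 35% and 8/20 = 40%, 11/20 = 55% and 12/20 = 60%, 22/30 = 73.3% and 23/30 = 76.7%. This is not a finding.

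**Conclusion.** The inconsistency is real and follows from the article's own figures. At 48 site-months, a total of 16 is stop on 1a and proceed with modifications on 1b, and 29 is green on 1a and amber on 1b. The value 0.35 belongs to two bands, which affects 17 if rates are rounded to two decimals. The article states no precedence between the rows.

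The 48 site-month result assumes that all four sites are open for all 12 months and that the red total means 15 or fewer. Any larger divergence rests on assumed opening delays, and much of it is the green-rate, amber-total pattern that can be read sensibly. These are stated thresholds for the primary objective, so they should be corrected, but the severity is minor to moderate.

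**What to change.** Edit the two recruitment rows of Table 2:

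1. Make the 1a bands contiguous and non-overlapping, and say whether the rate is compared rounded or unrounded.
2. Align 1a and 1b on one site-month denominator. For example, keeping the 1b totals at 48 site-months and using unrounded rates: green ≥0.625 (30 or more), amber above 0.3125 and below 0.625 (16–29), red ≤0.3125 (15 or fewer). Every total then has one colour on both rows.
3. State, before data are seen, how 1a and 1b combine or which governs when they differ. Step 2 alone is not enough: if the rate is computed on fewer than 48 site-months, the rows can still part. Which row governs is the sponsor's choice.

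The cost is table edits, with two shifts to declare. The green rate becomes slightly stricter (0.60 to 0.625, so 29 moves from green to amber on 1a). The red cut-off becomes slightly more lenient (16 moves from stop to amber on 1a). If the sponsor prefers to keep 0.35 as the stop rate, the alternative is to raise the 1b red total to 16 or fewer and start amber at 17, because 0.35 × 48 = 16.8.

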### Intervention: the EASE-CF programme

EASE-CF is a structured weight-loss programme delivered by a specialist CF dietitian to support adults with CF and excess weight to achieve weight loss of 5%–10% over a 24 week period. The intervention combines structured energy restriction (including a meal replacement product and a portion-controlled ready-prepared meal), individualised goal setting and accountability to a dietitian to promote dietary behaviour change, habit formation and increased self-efficacy.

As, to our knowledge, no previous trials of weight-loss programmes for people with CF have been conducted, the intervention was informed by evidence from other chronic health conditions, relevant study protocols and CF clinician input, including a previous qualitative study exploring CF clinicians’ views on this topic^16^ and a survey of current dietetic practice for overweight and obesity.^17^ A group of people with lived experience of CF and excess weight also helped to shape the research question and inform the mode, delivery and length of the intervention.

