The programme includes an initial 60 min consultation to assess dietary patterns and social circumstances, introduce the programme and establish personalised goals, followed by weekly 20 min video consultations to review progress, support self-monitoring of weight, reinforce behaviour change strategies, address barriers, provide accountability and facilitate action planning. The frequency of sessions may be reduced to fortnightly, based on mutual agreement between the dietitian and the participant if the participant is progressing sufficiently towards their weight loss target. Participants continue routine CF dietetic care as these include assessment of other clinical issues not included in the EASE-CF programme. Dietitians delivering the intervention are registered dietitians working within specialist CF services. All study dietitians receive a 2-hour study-specific training session prior to delivering the intervention covering the intervention protocol, behaviour change components and delivery procedures, together with a detailed programme manual and access to central support where required. The dietary component comprises three eating occasions per day (~1300 kcal/day). This standardised prescription was selected to maximise intervention fidelity and simplify delivery within this feasibility study. Participants are monitored throughout the intervention, and dietary adjustments may be made where necessary based on weight loss progress, tolerability and clinical considerations. Each day participants will be asked to consume: (1) A meal replacement product (shake/porridge of 200 kcal, Habitual Healthcare), (2) A portion-controlled high-protein ready meal of up to 600 kcal (Frive) and (3) An additional meal chosen by the participant based on dietitian’s advice for healthful eating. Water or no/low-calorie drinks are advised, with up to two snacks (one high-protein energy-restricted snack and one portion of fruit). The meal replacement products and ready meals are purchased using study funding and provided to participants free of charge. The manufacturers have no role in the study design, data collection, analysis, interpretation or publication of results.

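### The engagement criterion states two thresholds, ten sessions and 60% of sessions, that disagree on the weekly schedule, and does not say which governs

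*Protocol article*

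**What the plan says.** Table 2 of the protocol article, and the list beneath it under Primary feasibility outcomes, classes a participant as engaged if he or she "attended ten or more sessions during the 24 weeks (60% of sessions"), "inclusive of at least one of the last three sessions". The traffic-light bands then apply to the proportion of participants who meet that definition: green from 60%, amber "36%–59% (consider modifying based on process evaluation"), red at 35% or below.

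The schedule is in the section on the EASE-CF programme. "The programme includes an initial 60 min consultation", "followed by weekly 20 min video consultations to review progress". The programme is meant "to achieve weight loss of 5%–10% over a 24 week period". There is one permitted departure from weekly contact: "The frequency of sessions may be reduced to fortnightly, based on mutual agreement between the dietitian and the participant", and only "if the participant is progressing sufficiently towards their weight loss target".

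The article gives no planned total number of sessions.

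**The concern.** The definition treats ten sessions and 60% of sessions as the same bar. Weekly contact for 24 weeks gives far more than the 16 or 17 sessions needed for that to be true. Anyone applying the criterion therefore has two rules to choose from, and for a participant who stays weekly they differ by five sessions.

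The step-down adds a second difficulty, because the number of sessions offered then varies between participants. It is open only to those progressing well, so a fixed count asks for a larger share of sessions from the people who are responding to the programme.

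Engagement is one of the criteria that determine whether a definitive trial goes ahead, and a red result means it does not. If the choice between count and percentage is left until attendance is known, the criterion is no longer fully pre-specified.

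**Working it through.** **Inputs.** Programme length 24 weeks, one initial consultation, weekly sessions by default, fortnightly by agreement (EASE-CF programme section). Threshold of ten sessions, stated as 60% (Table 2 and text). Intervention arm of 20 (Sample size).

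**Step 1: try to reproduce the 60%.** The share is 10/D, where D is the number of sessions offered.

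- Weekly, initial consultation not counted: 10/24 = 41.7%.
- Weekly, initial consultation counted: 10/25 = 40.0%.

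The 60% is not reproduced. In reverse, 0.60 × 24 = 14.4, which rounds up to 15 sessions, and 0.60 × 25 = 15.

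**Step 2: find the D that would make it true.** 10/0.60 = 16.7. The nearest whole numbers are 10/16 = 62.5% and 10/17 = 58.8%.

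**Step 3: see whether the step-down can give that D.** With weekly sessions to week w and fortnightly ones to week 24, D = w + (24 − w)/2 = 12 + w/2, or 13 + w/2 with the initial consultation. Setting D = 16.7 gives w of about 9 without the initial consultation and about 7 with it.

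| Schedule | D without / with initial | Ten as a share | Sessions needed for 60% |
|---|---|---|---|
| Weekly throughout | 24 / 25 | 41.7% / 40.0% | 15 / 15 |
| Fortnightly after week 12 | 18 / 19 | 55.6% / 52.6% | 11 / 12 |
| Fortnightly after week 8 | 16 / 17 | 62.5% / 58.8% | 10 / 11 |
| Fortnightly after week 4 | 14 / 15 | 71.4% / 66.7% | 9 / 9 |
| Fortnightly throughout (bound only) | 12 / 13 | 83.3% / 76.9% | 8 / 8 |

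The last row is a limit, not a realistic case, since sessions start weekly.

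**Step 4: classify two participants, counting the initial consultation.**

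- Weekly throughout, 10 of 25 attended: 40%. Engaged by the count, not by the percentage.
- Stepped down after week 4, so 1 + 4 + 10 = 15 offered, 9 attended: 60%. Engaged by the percentage, not by the count.

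Both are assumed to have attended at least one of their last three sessions.

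**Step 5: illustrate the possible effect on the traffic light.** With 20 in the intervention arm, green needs 0.60 × 20 = 12 engaged, and red is 0.35 × 20 = 7 or fewer. The documents give no attendance rate, so suppose each session is attended independently with probability p, all participants stay weekly (D = 24), and the last-three condition is ignored. The binomial probabilities of being engaged, read as expected proportions, are:

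| p | Ten or more | Fifteen or more | Band by count / by percentage |
|---|---|---|---|
| 0.4 | 0.51 | 0.02 | amber / red |
| 0.5 | 0.85 | 0.15 | green / red |
| 0.6 | 0.98 | 0.49 | green / amber |
| 0.7 | 1.00 | 0.85 | green / green |

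The choice of rule changes the expected band for p from 0.4 to 0.6 and not at 0.7. This is an illustration, not a forecast.

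**The case against.** The best defence is that the count of ten is the operative rule and the bracket only glosses it. Read that way, the criterion can be computed today: ten or more sessions plus one of the last three. The bands cut the share of participants, so the 60% in the bracket never enters the banding.

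The gloss may also have had a basis. Step-down is part of the design, so the average participant may be offered fewer than 24 sessions, and a move to fortnightly at around week 7 to 9 would make ten about 60%. The article is condensed and mentions a programme manual that is not shown, which could hold such an expectation. Finally, a fixed minimum number of contacts is a legitimate way to define engagement. That it represents a different share for different people is a design trade-off, not an error.

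Much of this stands. A reader might infer from the mismatch that the go/stop decision itself rests on a wrong figure, or that ten sessions can never be 60%. The documents support neither. What the defence does not remove is that the article states the percentage twice, beside a weekly schedule on which it is untrue, gives no total of 16 or 17, and does not say that the count prevails. Step-down is conditional and individual, so it cannot justify one percentage for everyone.

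**Conclusion.** The point holds as an internal inconsistency in a primary progression criterion. On the default schedule the stated 60% is really 40% to 42%, and a true 60% would be 15 sessions, five more than the count. Count and percentage roughly agree only when 16 or 17 sessions are offered, which the article permits but nowhere states. Above that number the count is the easier bar; below it the percentage is.

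The share calculations rest only on the article's own schedule, and whether the initial consultation counts makes little difference. The effect on the traffic light depends on attendance and on how many participants step down, neither of which is known, so its size and direction are not established.

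**What to change.** Before attendance data are reviewed, let one threshold govern, in Table 2 and in the matching text. Either of these would do:

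- Define an engaged participant as one who attended at least 60% of the sessions scheduled for that person under the agreed frequency, including at least one of that person's last three scheduled sessions.
- Keep the count of ten and replace the bracketed 60% with the correct share, about 40% of a weekly schedule. This accepts that participants who step down early must attend a larger share.

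In both cases, state whether the initial consultation counts, and name all participants randomised to the intervention as the denominator. The Engagement row says only participants, whereas the Adherence row specifies the intervention group.

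The cost is a sentence or two. Attendance at scheduled dietetic appointments is already to be collected, though the first option also needs the agreed frequency, and the date it changed, for each participant. Under that option the bar rises from 10 to 15 sessions for those who stay weekly and falls for those stepped down early (to 9 in the week-4 example), so the engagement result could move either way.
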